(1) Primary indicators: average daily gaming time (self-reported by participants), Five Facet Mindfulness Questionnaire (FFMQ), Internet Addiction Test (IAT), Game Craving Scale (adapted from QSU-Brief), Adolescent Executive Functioning Scale (EFS-A), Barratt Impulsiveness Scale, State Mindfulness Scale, Game Craving Visual Analogue Scale, behavioral data, and EEG data (from EEG equipment).

(2) Secondary indicators: Self-Rated Sleep Status Scale, Depression-Anxiety-Stress Scale (DASS-21), Positive and Negative Affect Schedule (PANAS).

(3) Safety indicators: Researchers will inquire daily during the intervention period whether participants experience any adverse reactions. If there are any adverse reactions, they will communicate in person or by phone with the research staff.

Measurement time points are detailed in item 5.

1. ***Definition of Participant Effectiveness Determination. [This includes definitions for participant withdrawal, exclusion, loss to follow-up, confounding factors, study discontinuation, and study suspension]***

(1) Participant Withdrawal: Each participant can withdraw from the study at any time during the experiment without providing any reason. Participants who withdraw voluntarily will not be included in the analysis. Under the conditions of a mixed study, we have a complete access procedure for withdrawn participants. If participants are willing to provide a reason for their withdrawal, it will be recorded by the researchers.

(2) Participant Exclusion: If participants cannot consistently participate in the group interventions during the training process—where the focused breathing meditation training lasts one week—those who attend fewer than 5 sessions will be considered not fully intervened and should theoretically be excluded or adjusted using a mixed-effects model.

(3) Participant Loss to Follow-up: If any participant cannot be contacted for two consecutive attempts after the intervention is completed, they will be classified as lost to follow-up.

(4) Participant Contamination: After the intervention is completed, we will conduct a census of participants. If any participant in the control group attempts to learn about the training methods of the intervention group (or vice versa) and tries to train, they will be classified as contaminated participants.

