(5) Participant Termination: To ensure the health of the participants, any adverse events will constitute a termination condition. Researchers will discuss such situations with the affected participants to consider premature termination of their intervention. Appropriate clinical interventions will be provided to them with their consent.

(6) Participant Suspension: In this trial, we will allow participants to request suspension of their involvement in the intervention. If any requests for suspension are made, participants will be moved to a future intervention group after the trial team assesses that no adverse events or reactions have occurred. Data collected from these participants during the current trial will not be included in the final data analysis.

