For power spectrum and functional connectivity analysis: EEG data will calculate the relative power of six EEG frequency bands at the single electrode and ROI levels (δ: 1-4Hz, θ: 4-8Hz, α: 8-13Hz, low β: 13-20Hz, high β: 20-30Hz, low γ: 30-48Hz). Phase Locking Value (PLV) and Phase Lag Index (PLI) will be calculated using the FieldTrip toolbox. Source localization analysis will be used to explore functional changes in subcortical regions.

For ERP data, we selected the N2 and P3 components based on previous research. The analysis epoch will be 1000ms, with the baseline being the 200ms before stimulus presentation. The N2 negative component is primarily induced by the frontal central region, so the frontal midline electrodes were chosen as the region of interest. The time window for N2 is 250-350ms post-stimulus lock, while P3 is a positive component appearing in the parietal mid/post region, with the parietal electrodes selected as the region of interest, and the time window is 300-400ms post-stimulus presentation. To avoid Type I error rates, we did not analyze individual electrodes; instead, we averaged the amplitude values of the electrodes within the selected time window as the dependent variable for analysis. All work related to ERP component analysis was conducted using ERPLAB.

Finally, we will simultaneously conduct ITT analysis for this study, considering dropout levels as a very important indicator for recording and analysis, attempting to objectively reveal the intervention effects of focused breathing meditation training on executive function from both ITT and PP analysis perspectives..

1. ***Participant management system.***

(1) Contact and Guidance: A contact group composed of relevant researchers is responsible for providing guidance or answers to all research-related content or questions encountered by participants throughout the duration of the study. This ensures that participants have a sufficient understanding of the research and can better cooperate with the process. Researchers must promptly address and record any instances of withdrawal, removal, loss to follow-up, termination, or suspension involving participants.

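### The withdrawal and suspension rules remove randomised participants without confining this to a per-protocol set, so the promised ITT analysis cannot be carried out as written

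*Protocol*

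**What the plan says.** Under Definition of Participant Effectiveness Determination, the protocol sets three rules that act on people after grouping.

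- Item (1), withdrawal, which is allowed at any time: "Participants who withdraw voluntarily will not be included in the analysis".
- Item (2), low attendance: "those who attend fewer than 5 sessions will be considered not fully intervened and should theoretically be excluded or adjusted using a mixed-effects model".
- Item (6), suspension: "participants will be moved to a future intervention group after the trial team assesses that no adverse events or reactions have occurred". It then adds: "Data collected from these participants during the current trial will not be included in the final data analysis".

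The last paragraph of Statistical analysis methods commits to something different: "we will simultaneously conduct ITT analysis for this study, considering dropout levels as a very important indicator for recording and analysis", with the intervention effect to be viewed "from both ITT and PP analysis perspectives".

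Methods of randomization and concealed allocation, item (1), places grouping after baseline collection. Study design states a superiority aim against the control group.

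**The concern.** An ITT analysis takes everyone randomised, in the arm allocated. Items (1) and (6) take people out of the analysis because of what they did after allocation, and neither item says that this applies only to a PP set. If both are followed, the set labelled ITT is no longer the randomised set. It would differ from the PP set only through whatever non-adherers remain.

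The rules also delete data rather than merely accept missing data. Follow-up runs from the post-intervention visit to one year. Read literally, a participant who finishes training, gives the post-intervention Stroop measurement and withdraws months later loses that observed outcome.

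The attendance rule adds a choice that is never made. Excluding low attenders and adjusting for them are different analyses, and nothing says which applies or when that is decided. The Blinding section concedes that researchers are hard to blind, so an open choice of this kind is undesirable.

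At stake is the randomised comparison on which the superiority claim rests. If leaving is related to outcome and differs between arms, the retained groups are no longer comparable.

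**Working it through.** **1. The plan's own figures.** Sample size estimation gives a 125 ms reduction, SD 250 ms, two-sided alpha 0.05, power 0.80 and a paired t-test. Then d = 125/250 = 0.5 and n = 33.4, rounded up to 34, as stated. The 20% dropout allowance gives 34 x 1.2 = 40.8, so 41, as stated. (Dividing instead, 34/0.8 = 42.5, gives 43; that difference does not affect this point.) If the same 20% applied to all 122 participants, an assumption, about 0.20 x 122 = 24 people could fall under these rules.

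**2. The statements side by side.**

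- Withdrawn: out of the analysis, no qualifier. Incompatible with ITT.
- Suspended: data out of the final analysis, no qualifier, and the person moves to a later group. Incompatible with ITT.
- Fewer than 5 sessions: excluded or adjusted. The first option conflicts with ITT if it is applied there; the second need not.
- Analysis section: ITT and PP both promised, with no statement that the exclusions belong to PP.

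This contradiction is textual and needs no arithmetic.

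**3. How large a bias could be.** The documents give no attendance distribution and no link between attendance and outcome, so what follows is illustration. Assume no true effect, SD 250 ms, the lowest-attending share f removed from one arm only, and correlation rho between attendance and outcome under bivariate normality. The retained mean shifts by

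shift = rho x phi(z_f) / (1 - f), in SD units.

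- f = 0.10: phi = 0.1755, and 0.1755/0.9 = 0.195. With rho = 0.3, 0.058 SD = 14.6 ms; with rho = 0.5, 0.097 SD = 24.4 ms.
- f = 0.20: phi = 0.2800, and 0.2800/0.8 = 0.350. With rho = 0.3, 0.105 SD = 26.2 ms; with rho = 0.5, 0.175 SD = 43.7 ms.

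The range is about 15 to 44 ms, which is 14.6/125 = 12% to 43.7/125 = 35% of the target effect. With rho = 0, or with the same share removed in the same relation to outcome in both arms, the bias is 0.

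**4. Effect on the false-positive rate.** Assume 41 per arm, no true effect, and a share q removed from one arm only whose mean is D SD worse than those retained. The bias is q x D x 250 ms. It is compared with a standard error of 250 x sqrt(1/(41(1 - q)) + 1/41) in a normal approximation.

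- q = 0.10, D = 0.25 to 1.0: bias 6 to 25 ms, two-sided rejection rate 5.1% to 7.3%.
- q = 0.20, D = 0.25 to 1.0: bias 12.5 to 50 ms, rejection rate 5.5% to 13.7%.
- q = 0.30, D = 0.25 to 1.0: bias 19 to 75 ms, rejection rate 6.1% to 23.4%.

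At the mild end the rate is barely above the nominal 5%.

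**The case against.** The best defence is that the exclusions were meant for the PP analysis, which the protocol does plan, and that a SAP may define the sets. A SAP could indeed name the primary set and fix the model, and their absence here is not a fault. It could not, however, honour both items (1) and (6) and the ITT promise, because the protocol states those exclusions without any limit. If PP was meant, the text has to say so.

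Four stronger readings are tempting, and the documents do not support them.

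- A reader might infer that low attenders are simply dropped. The text says they "should theoretically be excluded or adjusted using a mixed-effects model", and adjustment would keep them in. The defect is an unresolved rule.
- A reader might infer that the 5-session rule filters the mindfulness arm only. The sentence does mention the breathing-meditation week, but it opens with participation in the group interventions in general, and the control arm also receives training. The supportable criticism is that its scope is unclear.
- A reader might infer that the bias is certain and favours mindfulness. The withdrawal and suspension rules apply to everyone, and nothing in the protocol says which arm will lose more people or how they differ. The direction could go either way, and the bias can be nil.
- A reader might infer that suspended people re-enter as new cases. The protocol says they move to a later group and is silent on whether they are counted again.

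The use of data after withdrawal also depends on consent terms, which are not among the pages available. That limits the fix but leaves the contradiction in place.

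**Conclusion.** The point stands in this form: the withdrawal and suspension rules, as worded, make the promised ITT analysis impossible and discard outcomes already collected. The attendance rule is left open, both in what is done and in which arms it covers. This rests on the text alone and should be corrected before the trial is analysed.

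The resulting bias is a risk whose size and direction cannot be derived from the documents. It ranges from nil, if exclusions are non-differential, to about 15-44 ms against the 125 ms target. The upper range requires actual exclusion of 10-20% from one arm only and an attendance-outcome correlation of 0.3-0.5; all of these are assumptions.

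**What to change.** Reword the Definition of Participant Effectiveness Determination and Statistical analysis methods sections so that they agree:

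- State that the ITT analysis includes everyone randomised, in the allocated arm, using all data collected up to withdrawal or suspension, and later visits where the participant agrees, subject to the consent terms.
- Confine the withdrawal, suspension and attendance exclusions to a predefined, supportive PP set, and apply the same attendance rule in both arms.
- Replace the exclude-or-adjust alternative with that single rule.
- Count each suspended participant once, under the arm first allocated.

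Participants' freedom to withdraw or suspend is untouched; only the handling of their data changes. The cost is protocol wording and slightly more analysis work, with a possibly smaller estimated effect.

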Through the use of scales, behavioral data, and EEG data, this study aims to investigate whether the three sub-components of executive function in individuals with internet gaming addiction are impaired. Furthermore, it will conduct a one-week focused breathing meditation intervention to explore the effectiveness of concise mindfulness on executive function and its impact on brain function mechanisms. This endeavor will provide more targeted intervention strategies for research into executive function.

1. ***Inclusion and exclusion criteria. [Inclusion criteria define the main body of the study and determine the representativeness of the study population; exclusion criteria define individuals within the study population that may affect the study and determine the homogeneity of the study population]***

Inclusion criteria:

(1) Right-handedness;

(2) Normal vision or corrected-to-normal vision;

(3) Age between 18 and 40 years;

(4) Good mental and physical health (PHQ-9 total score < 20, GAD-7 total score < 11);

(5) Absence of other addictions (e.g., smoking, alcohol, gambling);

(6) For individuals with internet gaming disorder (IGD): Internet Addiction Test (IAT) score ≥ 50, DSM-5 score ≥ 5, gaming history exceeding 2 years, and gaming time of more than 14 hours per week;

(7) For recreational gamers: IAT score < 50, DSM-5 score < 5.

Exclusion criteria:

(1) Individuals with asthma, epilepsy, or a history of mental illness;

(2) Those who have taken steroid medications within the past three months;

(3) Individuals who have practiced meditation, yoga, Tai Chi, or Qi Gong for more than 20 hours in the past year or throughout their lifetime, attended meditation or yoga retreats, or participated in any meditation courses;

(4) Individuals unsuitable for electroencephalogram (EEG) testing due to metal implants, severe head injuries, contact dermatitis, or silicone allergies;

(5) Those with a PHQ-9 total score ≥ 20 or a GAD-7 total score ≥ 11;

(6) Individuals with other addictions (such as smoking, alcohol, or gambling);

(7) Individuals with strong adherence to a particular religious belief that would interfere with their ability to participate in the required meditation exercises;

(8) Individuals currently participating in similar trials or other neurophysiological studies.

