(1) In this study, the intervention period focused on breath meditation lasts for one week and serves as a concise mindfulness behavior training. The study will involve a baseline collection of EEG and other relevant data for all participants, a one-week training on the intervention content, collection of post-intervention EEG and other relevant data, and follow-ups (one week, one month, four months, six months, and one year after data collection post-intervention). During the follow-up phase, participants will undergo multiple mindfulness training sessions. Grouping will occur after the baseline data collection for participants is completed.

(2) The breath meditation training is the primary intervention method employed in this study. The design includes grouping into an experimental group and a control group: the experimental group (breath meditation training) and the control group (relaxation training). The recruited participants are from the same school, and their connections make it challenging to implement the criteria for double-blind randomization.

(3) The randomization process for this trial will utilize the random sequence generator available at random.org.

1. ***Blinding. [Blinding is used in treatment studies and diagnostic trials to reduce the risk of implementation bias and measurement bias. Implementing strict confidentiality measures, such as using placebos or simulating procedures, is an effective blinding method. If blinding is necessary and feasible for your study, describe the methods and procedures for implementing blinding]***

This trial involves group therapy, with participants being students from the same school. Therefore, it is possible that among participants who may know each other or even among those who do not, conversations related to the experimental training they are undergoing may arise. Additionally, maintaining blinding for the researchers is quite challenging, as they can easily be influenced by information related to the experiment during the process. As a result, it is not feasible to meet the double-blind requirements of clinical trials.

1. ***Outcome Measures. [Outcome measures are used to evaluate the results of a study and can include primary, secondary, and safety measures, including adverse events and reactions. Please describe the names of the measures, the methods of measurement, and the time points at which they are assessed]***

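### The suspension rule does not keep participants in their randomised arm and drops their data, so the randomised comparison suffers whether the later group lies inside or outside the trial

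*Protocol*

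**What the plan says.** All references are to the protocol.

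- **Suspension.** Item (6) of Definition of Participant Effectiveness Determination lets participants ask to suspend their part in the intervention. They are then handled as follows: "participants will be moved to a future intervention group after the trial team assesses that no adverse events or reactions have occurred". The next sentence reads: "Data collected from these participants during the current trial will not be included in the final data analysis".
- **Timing and method of allocation.** Methods of randomization and concealed allocation states: "Grouping will occur after the baseline data collection for participants is completed". It adds: "The randomization process for this trial will utilize the random sequence generator available at random.org". It has no provision for someone who pauses and comes back.
- **Eligibility.** Exclusion criterion (3) has an hours limb, "Individuals who have practiced meditation, yoga, Tai Chi, or Qi Gong for more than 20 hours in the past year or throughout their lifetime", and a separate limb with no hours threshold, "attended meditation or yoga retreats, or participated in any meditation courses".
- **Analysis.** Statistical analysis methods commits to an ITT analysis alongside a per-protocol (PP) one.

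**The concern.** The rule acts on people who already have an arm. It moves them on one stated condition, the adverse-event check, and does not say that the arm they were randomised to goes with them. It also does not say whether the later group is part of this trial. Each way of filling that gap causes a problem. If returners are analysed in a later group, their arm may not be the one the random sequence gave them, and they are no longer naive to the tasks or, for some, to the training. If they are not analysed, the analysis loses people after allocation for a reason (asking to pause the training) that may well differ between meditation and relaxation. Neither loss can be repaired at the analysis stage.

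**Working it through.** The plan gives no figure for suspensions, so the check is mainly a comparison of passages.

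1. **Is suspension post-allocation?** Yes. Grouping follows baseline, and what is suspended is involvement in the intervention. Everyone covered by the rule has been allocated.

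2. **What decides where they go?** Item (6) names one condition, the adverse-event check. It does not mention the original arm, the random sequence, re-screening or a second baseline.

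3. **Which group is meant?** The Fig 3 legend sets the intervention group (mindfulness) against the control group (relaxation). Sample size estimation does the same, with 61 in each. Item (4) of the same list as the suspension rule contrasts the two terms again. On that usage, a suspended relaxation participant may be placed in mindfulness. The SPIRIT table, however, lists both trainings under interventions, so a later session group of either arm is also a possible meaning. The text permits the first reading and does not require it.

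4. **Does exclusion (3) reach a returner?**
   - *Hours limb.* The training is short: "the intervention period focused on breath meditation lasts for one week". Session number and length are not stated. Assuming at most 7 sessions of 15 to 60 minutes, exposure is 7 × 0.25 = 1.75 hours to 7 × 1 = 7 hours. Passing 20 hours would need more than 20 / 7 = 2.9 hours per session. Group sessions are unlikely to reach this; hours of self-practice are not given.
   - *Course limb.* There is no threshold. Standard operating procedures describes a week of teacher-led sessions, with each day's content sent out for further practice. If that counts as a course, a mindfulness participant who had begun it falls under this limb on re-entry. A relaxation participant does not.

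5. **Task practice.** Table 1 places behavioural and EEG data at both baseline time points, and the Fig 3 legend names the Stroop, shifting and N-back tasks. Suspended participants from either arm will have done these. Stroop reaction time is the indicator that sets the sample size.

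6. **The two readings of the future group.**

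| Reading | Consequence |
| --- | --- |
| Inside this trial | Task-practised people, some of whom may have started meditation, join a group with nothing tying them to their random assignment |
| Outside this trial | Allocated people are missing from the final analysis, against the ITT commitment |

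7. **Illustrative size.** The plan's denominators reproduce: 41 + 20 = 61 per arm, and 2 × 61 = 122. Assume that 2 to 10% suspend:
   - 0.02 × 122 = 2.4 and 0.10 × 122 = 12.2, so about 2 to 12 people. On the outside reading these are the people lost.
   - If half come from the mindfulness arm, about 1 to 6 could have had meditation training. Against 61 that is 1/61 = 1.6% to 6/61 = 9.8%. This is an upper figure, because some may pause before any session.

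**The case against.** The best reply is that item (6) is only loosely worded. It speaks of a future group and then of the current trial, which can be read as deferred training outside this dataset. It describes no second baseline and no re-enrolment. The team's only stated task is the adverse-event check, so silence about the arm does not show that the team chooses it. Entry criteria normally apply once, at enrolment; otherwise every mindfulness participant would breach exclusion (3) after starting.

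Much of this stands, and it rules out several stronger readings that a reader might infer:

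- *That exclusion (3) bars anyone with prior meditation training.* It does not. Practice alone counts only above 20 hours, and only the course limb could apply here.
- *That already-trained people definitely re-enter with a fresh baseline that shrinks their measured change.* Re-entry and a new baseline are both inferences, and the protocol gives no figure for a practice effect.
- *That movement runs one way, from either arm into mindfulness.* The wording allows this but does not establish it.
- *That 2/61 to 12/61, or 3 to 20%, of the mindfulness arm would be pre-exposed.* This counts relaxation participants as meditation-exposed. It also assumes that everyone returns, goes to mindfulness and is analysed, with the denominator fixed at 61.

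The reply does not rescue the rule. Taking the later group as outside the trial removes the re-entry problem only by accepting the loss of allocated participants, which the ITT commitment does not allow. Nor is this a detail left to a statistical analysis plan: it is an express protocol rule on what happens to randomised people and their data.

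**Conclusion.** The concern holds in a limited form. The suspension rule moves allocated participants on an adverse-event check alone, does not preserve their randomised arm, and removes their data. On either reading of the future group, the randomised comparison is weakened. The eligibility conflict is narrower: it concerns only mindfulness participants who had started training, only through the course limb, and only if the trial's own sessions count as a course and the later group is in the trial. Task practice from two baseline visits applies to returners from both arms.

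The size is unknown because the protocol gives no expected number of suspensions. The 2 to 12 people above rest wholly on an assumed 2 to 10% rate and only show the order of magnitude. The direction of any bias cannot be derived from the document.

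**What to change.** Reconcile exclusion criterion (3), item (6) on suspension and the ITT commitment in Statistical analysis methods by stating that:

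- a suspended participant keeps the original allocation, randomisation number and baseline, and is not re-enrolled or re-baselined;
- the participant is counted once, in the originally allocated arm, in the ITT analysis;
- any later training in the other arm is outside the trial data.

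Replace the sentence that drops these participants' current-trial data so that it agrees. Without that second change the first has no effect, because there would be no retained data to analyse. The adverse-event check and the decision on whether someone resumes training are clinical matters and stay as they are.

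The cost is a short text change, and Study design says that the trial has not yet started. There are two downsides. Suspended places are not refilled by the same people. The ITT set will also include some incompletely trained participants; the PP analysis already planned can address completed training separately.
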